## Abstract

**Background:**

Informal caregivers of patients with Amyotrophic Lateral Sclerosis (ALS) or Progressive Muscular Atrophy (PMA) face stressful demands due to severe impairments and prospect of early death of the patients they care for. Caregivers often experience feelings of psychological distress and caregiver burden, but supportive interventions are lacking. The objective of this study is to investigate the effectiveness of a psychosocial support program aimed at enhancing feelings of control over caregiving tasks and reducing psychological distress. This support program is based on an existing program for adult partners of people with cancer and is adapted to meet the needs of ALS caregivers.

**Methods:**

This study is a randomized controlled trial using a wait-list control design. One hundred and forty caregiver-patient dyads, recruited from a nationwide database and through the website of the Dutch ALS Center, will be either randomized to a support program or a wait-list control group. The blended intervention is based on Acceptance and Commitment Therapy and consists of 1 face-to-face contact, 6 online guided modules and 1 telephone contact. The intervention can be worked through in 8 weeks. The effectiveness and the participants’ satisfaction with the intervention will be evaluated using a mixed method design. Caregivers and patients will be asked to fill in questionnaires on 4 occasions during the study: baseline, 3 months, 6 months and 9 months. The main study outcome is the psychological distress of the caregiver assessed with the Hospital Anxiety and Depression Scale. Secondary outcomes are caregiver burden, caregiver quality of life, quality of life of the patient and psychological distress of the patient. Group differences in primary and secondary outcomes at 6 months will be compared with linear mixed model analysis. In a subgroup of caregivers we will explore experiences with the support program through semi-structured interviews. Usage of the online modules will be logged.

**Discussion:**

The study will provide insights into the effectiveness of a blended psychosocial support program on psychological distress of caregivers of patients with ALS or PMA, as well as into indirect relations with patients’ wellbeing.

**Trial registration:**

Netherlands Trial Registry NTR5734, registered 28 March 2016.

## Background

Informal caregivers, usually the patient’s partner, are key figures in Amyotrophic Lateral Sclerosis (ALS) and Progressive Muscular Atrophy (PMA) care. They provide the majority of support to patients and are often the primary caregivers. ALS and PMA are fatal motor neuron diseases, ALS affecting both upper and lower motor neurons while PMA only affects lower motor neurons. Informal caregivers of patients with ALS or PMA face stressful demands due to the prospect of an early death and severe impairments of the patient. Patients experience a progressive decline of muscle strength resulting in paralysis, difficulty with speech and swallowing, possible cognitive and behavioral problems and ultimately, respiratory failure leading to death [1–3]. Patients become increasingly impaired and the amount of care that is needed accumulates [4].

Since PMA is a rare subtype of motor neuron disease, research studies on PMA caregivers are limited. However, PMA shows substantial overlap with ALS and is considered to be a form of ALS [5]; PMA caregivers are, therefore, likely to struggle with the same issues as ALS caregivers. The wellbeing of ALS caregivers has been studied more intensively and shows that as the disease progresses, ALS caregivers experience heightened feelings of psychological distress and burden [6–8], which is related to a diminished quality of life [9]. The wellbeing of ALS caregivers is critical because a high level of burden might predict a breakdown in care, leading to earlier placement of the patient in a care-home or hospice [10].Therefore, improving the psychological health of the caregivers may not only improve their quality of life but also that of the patient.

Previous research has shown that psychological distress and feelings of burden of ALS caregivers are associated with disease characteristics of the patient (i.e. physical and behavioral problems) but also with characteristics of the caregivers themselves, such as their coping style or whether they find positive meaning in caregiving [7, 9, 11–15]. As the disease progresses, psychological and physical demands on the ALS caregiver increase. Patients become increasingly reliant on their caregiver, and caregivers have to take over responsibilities from the patient. Handling all these responsibilities, accepting a loved one’s illness and accepting the loss of the patient in the near future are examples of issues ALS caregivers struggle with [16].

ALS and PMA caregivers are faced with situations, yet may lack the relevant knowledge and skills, such as communicating about the disease and death, dealing with the patients’ behavioral changes, dealing with their own emotions or expressing their own boundaries [17]. Consequently, caregivers may not feel competent or in control with respect to their caregiving tasks, while the demands increase. From previous studies we know that a combination of high demands and feelings of insufficient control over caregiving is associated with poorer physical and psychological health outcomes of caregivers [18, 19]. Previous studies have indicated that there is a need for psychosocial interventions for caregivers, but such interventions are still lacking [6, 20, 21].

Acceptance and Commitment Therapy (ACT) is a form of cognitive behavioral therapy that encourages individuals to accept unwanted private events which are out of personal control (such as thoughts, feelings and memories) and to identify important values in life in order to engage in committed action to pursue these values [22]. The acceptance component in ACT makes this therapy valuable in contexts with circumstances that cannot be changed [23, 24], for instance, receiving a diagnosis of ALS or PMA. The values component supports caregivers to undertake action that is personally meaningful. This can assist them in adjusting to their situation, in moving on in life and in enhancing their psychological wellbeing [23]. Applying acceptance strategies and living up to personal values requires a different way of responding to situations and may increase the feeling of control [25].

ACT has proven to be effective in decreasing feelings of psychological distress in various target groups, including caregivers of other patient populations [26–28]. Recently, ACT has also been proved to be effective when delivered via the internet [28, 29]. Since ALS and PMA caregivers are often preoccupied with the care for their home-bound patient, receiving care in a more accessible and time efficient manner may offer opportunities.

In this study, we will investigate the effect of a blended support program in which face-to-face contact and e-health will be combined. The support program is based on Acceptance and Commitment principles and focuses particularly on the needs of ALS and PMA caregivers. This support program aims to diminish caregivers’ psychological distress by increasing their feelings of control in fulfilling the caregiving tasks for patients with ALS or PMA.

## Methods

The described protocol (Version 6, dated 27-07-2017) has been developed according to the Standard Protocol Items Recommendations for Interventional Trials (SPIRIT) and the Template for Intervention Description and Replication (TIDieR) [30, 31].

### Design

This study is a randomized controlled trial in which caregiver-patient dyads will be randomly allocated to one of two groups:Intervention group (support program during 8–12 weeks).Wait-list control group, receiving care as usual (6-month monitoring preceding the support program).

This design enables us to investigate whether offering a support program in addition to usual care improves the wellbeing of caregivers compared to care as usual. Both caregiver and patient will be asked to complete online questionnaires at baseline (T0), 3 months after baseline (T1), 6 months after baseline (T2) and 9 months after baseline (T3), but only the caregivers will receive the support program. In Fig. 1, the flowchart of the study is presented. In a subgroup of caregivers, we will explore experiences with the support program through interviews.

**Fig. 1 Fig1:**
[figure not shown]
Flowchart study

### Study population

Caregiver-patient dyads will be recruited through a nationwide ALS/PMA database and via the website of the Dutch ALS Center. The study will also be announced on websites of ALS/PMA patient associations. Patient and inclusion criteria are 1) the caregiver is the partner of the ALS or PMA patient; 2) the caregiver is 18 years or older; 3) caregiver and patient are proficient in Dutch to fill out the questionnaires; 4) caregiver and patient have internet access. When patients are not able or not willing to complete online questionnaires, caregivers are still eligible to join the support program provided the patient consents. The inclusion criteria remain in force.

### Sample size

The sample size calculation was based on Hospital Anxiety Depression Scale (HADS) data of informal caregivers in a previously completed study [6]. The total number of caregiver-patient dyads needed to detect a clinically relevant difference [32] of 3.65 points, with a standard deviation of 7.3 between the groups at T2, with an alpha of 0.05 and a power of 80%, is 116 caregiver-patient dyads (58 dyads in each group). Taking into account an attrition rate of 20%, we aim to include 140 caregiver-patient dyads in total.

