### Analyses

#### Statistical analyses

Descriptive statistics will be used to report demographic variables, clinical outcomes, and the use of the different modules. Group differences in primary and secondary outcomes will be compared with linear mixed model analyses, in which the mediator and covariates will be included. Statistical analyses will be performed primarily according to intention-to-treat and secondarily according to per-protocol principles. The intention to treat analyses will include data of all included caregivers, regardless of their adherence to the intervention or their missing data. In the per-protocol analyses we will only include caregivers who completed at least 4 modules (66.7%) and the T2 measurement. All hypotheses will be tested 2-sided, with a critical value of 0.05. Effect sizes on the primary outcome variable (HADS total) will be calculated with Cohen’s D using the means and pooled standard deviations of the two groups.

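### The stated inputs (3.65 points, SD 7.3, two-sided 5%, 80% power) require 64 caregivers per group; the stated 58 per group gives 76% power

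*Protocol article*

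**What the plan says.** The Sample size section of the protocol article gives every input for a comparison of two means. The target is a difference "of 3.65 points, with a standard deviation of 7.3 between the groups at T2". The significance level and power follow, with the result: "with an alpha of 0.05 and a power of 80%, is 116 caregiver-patient dyads (58 dyads in each group"). The section then inflates for loss: "Taking into account an attrition rate of 20%, we aim to include 140 caregiver-patient dyads in total".

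Sidedness is fixed in the Statistical analyses section: "All hypotheses will be tested 2-sided, with a critical value of 0.05". The same section plans linear mixed models that include covariates. Neither section gives a baseline correlation, a proportion of variance explained or a repeated-measures gain as an input to the sample size.

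**The concern.** A difference of 3.65 with an SD of 7.3 is half a standard deviation. The usual requirement for that effect, at two-sided 5% and 80% power, is 63 or 64 per group. The stated 58 is five or six per group lower, which is more than rounding or the choice between the normal and t formulas can explain.

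This calculation is the only justification given for the size of the trial. It concerns the primary outcome and a difference that the protocol calls clinically relevant. If the result does not follow from the inputs, the chance of missing that difference is larger than the 20% claimed. The Discussion already warns that better usual care may make a difference harder to show, so a non-significant result is foreseeable. Readers would then judge it against a power that the stated inputs do not support.

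**Working it through.** **Inputs, all from the protocol article**

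- Difference at T2: 3.65 points (Sample size)
- SD: 7.3 (Sample size)
- Alpha: 0.05 (Sample size), two-sided (Statistical analyses)
- Power: 80% (Sample size)
- Allocation: equal, 58 per group (Sample size)
- Attrition: 20%, target 140 (Sample size)

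**Step 1. Standardised difference.** d = 3.65 / 7.3 = 0.50.

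**Step 2. Attempt to reproduce 58 per group.** Normal approximation: n per group = 2 × ((z for alpha + z for power) / d)².

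- Two-sided 5%: 2 × ((1.960 + 0.842) / 0.50)² = 62.8, so 63 per group (126 in total).
- Two-sided 5%, noncentral t: 63.8, so 64 per group (128 in total).
- One-sided 5%: 50 (normal) or 51 (t) per group.

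None of these gives 58. Against the t-based total, 116 is 128 − 116 = 12 dyads short, or 12/128 = 9%.

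**Step 3. Power at 58 per group.** Noncentrality = d × √(n/2) = 0.50 × √29 = 2.693.

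- Two-sided, normal: Φ(2.693 − 1.960) = 76.8%.
- Two-sided, noncentral t: 76.1%.
- One-sided: 85.3% (normal) or 84.9% (t), so a one-sided test would overshoot 80%.

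**Step 4. What would make 58 right (two-sided, 80% power).**

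- A larger difference: 3.83 points by the t-test (0.525 SD), or 3.80 by the normal approximation.
- A smaller SD: about 7.02 by the normal approximation.
- A baseline adjustment that multiplies the variance by 1 − r²: r = √(1 − 58/63.77) = 0.30 by the t-test, or √(1 − 58/63) = 0.28 by the normal approximation.

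**Step 5. Does the recruitment target absorb the gap?** 116 × 1.2 = 139.2, which rounds to the stated 140. To keep 116 after a 20% loss needs 116 / 0.8 = 145. With 140 recruited, 140 × 0.8 = 112 remain, or 56 per group.

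| Evaluable per group | Power, t-test | Power, normal | Difference detectable with 80% power (t) |
|---|---|---|---|
| 56 (140 less 20%) | 74.6% | 75.4% | 3.90 |
| 58 (as stated) | 76.1% | 76.8% | 3.83 |
| 64 (required) | 80.1% | 80.7% | 3.64 |
| 70 (140, no loss) | 83.6% | 84.1% | 3.48 |

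To have 128 evaluable dyads after a 20% loss would take 128 / 0.8 = 160.

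**The case against.** The strongest reply is that 76% is the power of an unadjusted t-test at T2, which is not the planned analysis. The plan is a linear mixed model with covariates, and the caregiver HADS is measured at T0, T1, T2 and T3. If baseline HADS enters the model, modest correlations restore the power at 58 per group. The article gives no six-month correlation, so the following is an assumed range: r = 0.3 gives 79.9%, r = 0.4 gives 83.0% and r = 0.5 gives 86.9%. The test–retest values of .86 to .91 quoted for the HADS are not six-month correlations, but 0.30 is a low bar beside them. The intention-to-treat analysis also keeps caregivers with missing data, so those lost before T2 may still contribute, and with no loss at all 70 per group would exceed 80%. Finally, an article condenses a fuller protocol, and the shortfall is only about 4 percentage points.

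Much of this is fair. The power actually achieved may well reach 80%, and nothing here biases the estimate or invalidates the trial. But the Sample size section names no correlation or adjustment, and the Statistical analyses section does not name baseline HADS among the covariates. Condensing a protocol can excuse a missing detail. Here the article gives what reads as a complete set of inputs and a result that does not follow from them. If an adjustment was used, the input that determines the answer is absent; if it was not, the number is wrong. The hope of lower attrition is no rescue either, because the protocol itself plans for 20%.

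**Conclusion.** The concern holds. From the stated inputs, 80% power needs 64 caregivers per group (128 in total), and the stated 58 per group gives 76.1%. The chance of missing the stated 3.65-point difference is therefore 24%, not 20%. At the protocol's own attrition (56 per group) it is about 25%.

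These figures assume an unadjusted two-sided comparison of means at T2 with a common SD of 7.3, which is what the Sample size section describes. The normal approximation changes them by less than one percentage point and leads to the same conclusion. With a baseline adjustment and a T0–T2 correlation of 0.30 or more, 58 per group would be adequate, but the article does not claim this. The error is modest in size, but it lies in the trial's stated power and should be corrected.

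**What to change.** Correct the sentence in the Sample size section in one of two ways.

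1. **Keep the inputs and restate the power.** Say that 58 evaluable caregivers per group give 76% power for 3.65 points, or 80% power for 3.83 points. Add the figure that matches the recruitment plan: 140 recruited with 20% loss leaves 56 per group, with 75% power for 3.65 points, or 80% power for 3.90 points.
2. **Document the adjustment, if one was used.** Say that the calculation is for the baseline-adjusted comparison at T2, give the T0–T2 HADS correlation observed in the earlier caregiver study, and name baseline HADS as a covariate in the primary model. The correlation must come from those data and not be chosen to give 58. It has to be at least 0.30 for 58 per group, or about 0.35 for 56 per group (√(1 − 56/63.77) = 0.35).

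The first option costs one sentence and a slightly less favourable stated power. The second also needs a line in the Statistical analyses section. Neither changes enrolment.

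### With the stated 20% attrition, 140 dyads leave 112 at T2, not the 116 that the sample-size section requires

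*Protocol article*

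**What the plan says.** The Sample size section of the protocol article plans for a "clinically relevant difference [32] of 3.65 points" on the HADS, "with a standard deviation of 7.3 between the groups at T2", "with an alpha of 0.05 and a power of 80"%. The number needed on these inputs "is 116 caregiver-patient dyads (58 dyads in each group"). The next sentence sets recruitment: "Taking into account an attrition rate of 20%, we aim to include 140 caregiver-patient dyads in total". No inflation formula is given.

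The Abstract (Methods) repeats the target: "One hundred and forty caregiver-patient dyads". It also gives the time point of the comparison: "Group differences in primary and secondary outcomes at 6 months will be compared with linear mixed model analysis". The Statistical analyses section fixes the sidedness: "All hypotheses will be tested 2-sided, with a critical value of 0.05".

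**The concern.** An attrition allowance exists so that the required number remains after the expected loss. Here the required number (116), the expected loss (20%) and the recruitment target (140) stand in two adjacent sentences, and the three cannot all hold. A reader will take it that recruiting 140 protects the planned comparison at T2 against a 20% loss. On the protocol's own figures it does not.

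The pattern is familiar: the required number seems to have been increased by 20% when it should have been divided by the 80% expected to remain. What is at stake is the accuracy of the stated evaluable sample and, to a small extent, of the stated power.

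**Working it through.** **Inputs.** From Sample size: difference 3.65, SD 7.3 (standardized difference 3.65/7.3 = 0.50), alpha 0.05, power 80%, required number 116 (58 per group), attrition 20%, target 140. From Statistical analyses: two-sided testing.

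**1. Reproducing the target of 140.**
- Required number × (1 + attrition): 116 × 1.2 = 139.2, rounded up to 140. This reproduces the target.
- Required number / (1 − attrition): 116/0.80 = 145. This does not. For equal arms, 58/0.80 = 72.5, so 73 per arm and 146 in total.

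**2. What 140 delivers.**
- Remaining after 20% loss: 140 × 0.80 = 112, or 56 per group. Shortfall: 116 − 112 = 4 dyads, 2 per group.
- Attrition at which 116 would remain: 1 − 116/140 = 17.1%.

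**3. Cost in power of the attrition step alone.** Two-sided two-sample t-test, 2n − 2 degrees of freedom, noncentrality 0.50 × √(n/2):

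| n per group | Noncentrality | Power (t-test) | Power (normal approximation) |
|---|---|---|---|
| 58 | 2.69 | 76.1% | 76.8% |
| 56 | 2.65 | 74.6% | 75.4% |

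Going from 58 to 56 per group costs about 1.5 percentage points. At 56 per group, 80% power is reached at a standardized difference of 0.534, that is 0.534 × 7.3 = 3.90 points.

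**4. The rest of the gap to 80%.** This is a separate matter. The normal approximation gives n per group = 2 × (1.960 + 0.842)² / 0.50² = 62.8, so 63 per group (126 in total). The t-test gives 64 per group (128 in total). One-sided testing gives 50 or 51 per group, so it does not explain 58 either. The difference between 80% and 76.1% therefore belongs to the 116, not to the attrition step. With both steps corrected, the target would be 126/0.80 = 157.5, so 158, or 128/0.80 = 160.

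**5. Whether baseline adjustment could close the gap.** Adjusting for baseline HADS multiplies the residual variance by about 1 − r², where r is the T0–T2 correlation. At 56 per group, 80% power needs √(1 − r²) = 0.50/0.534, which gives r of about 0.35. Power is 79.9% at r = 0.35 and 80.3% at r = 0.36. The protocol states no value of r, so this is a break-even value and not an estimate.

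**The case against.** The strongest reply is that the primary intention-to-treat analysis is a linear mixed model that includes all caregivers whatever their missing data. Caregivers without a T2 value still contribute through T0 and T1. That stands in part: the 74.6% describes an unadjusted comparison of caregivers observed at T2, and so only approximates the power of the planned model. It does not repair the sample-size text, which counts dyads needed at T2 and makes an explicit allowance for losing some of them.

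Second, the period to which the 20% applies is not stated, and follow-up runs to T3 at 9 months. If the 20% covers all nine months, the loss by T2 could be 17.1% or less, and 116 would remain. Because the allowance directly follows a T2 requirement, loss by T2 is the more natural reading, but it is an assumption.

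Third, the multiplication by 1.2 is inferred. It fits exactly, but the document supports no more than "consistent with". The finding does not depend on it, because 140 × 0.80 = 112 whatever the route to 140.

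A reader might also infer that the attrition slip is what brings the trial from 80% power down to about 75%. The figures do not support that: about 1.5 points come from this step, and the remaining 4 or so from a required number that is too small. Charging the whole gap here would count it twice if the base number is also corrected. Nor can one infer that baseline adjustment already makes up the loss. Statistical analyses mentions a mediator and covariates, but baseline HADS is not among the covariates listed in Table 2, and no correlation is given.

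**Conclusion.** The point holds in a limited form. The figures 116, 20% and 140 are mutually inconsistent, and nothing elsewhere in the article reconciles them. If the 20% is lost by T2 in equal arms, the target leaves 112 dyads: 4 fewer than stated, and 5 to 6 below the recruitment figure that would deliver 116. The effect of this step on power is about 1.5 percentage points. The overall figure of about 75% power for 3.65 points also reflects the separate base-number error, and it applies to an unadjusted two-sided T2 comparison. This is a modest but certain arithmetic error in a figure that readers will rely on, and it should be corrected.

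**What to change.** Keep 140 and replace the attrition sentence with one that says what it delivers. For example: assuming the 20% loss occurs by T2, 112 caregivers (56 per group) are expected, which gives about 75% power for a difference of 3.65 points, or 80% power for about 3.9 points, in an unadjusted T2 comparison.

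If the authors would rather say that 140 allows 17% attrition with 116 remaining, they must in the same edit correct the power stated for 116 from 80% to about 76%. Otherwise the new wording keeps a wrong power claim.

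If they wish to claim that adjustment for baseline HADS restores 80% power, the text should name that adjustment and give the assumed T0–T2 correlation with its basis. At 56 per group the break-even is about 0.35 to 0.36.

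The cost is a rewording of the sample-size text and a slightly less favourable stated power. No extra enrolment is needed, and the 140 in the Abstract can stay.
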